**Inclusion criteria**
1.Patients with type 2 diabetes mellitus
2.Patients aged 70–85 years at enrollment
3.Patients with no or mild impairment of basic activities of daily living (Barthel Index score of 80 or more)
4.Patients with a Japanese version of the Montreal Cognitive Assessment score of less than 26
5.Mini-Mental State Examination score, between 21 and 30
6.Outpatients or those exhibiting a stable clinical course for more than 4 weeks after their last hospitalization or institutionalization and whose medical examination classification need no change during the monitoring period
7.Patients accompanied by a co-participant (study partner)
8.Those who gave written informed consent

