##### Improvement in Outcomes Related to T2DM

Metabolic control: In blood tests performed at baseline and 6-/18-month follow-up, the participants will be assessed for glycated hemoglobin (HbA1c), glycoalbumin, fasting blood glucose levels, and fasting blood insulin levels. Additionally, at baseline and 18-month follow-up, they will also be evaluated for SD of blood glucose levels, mean amplitude of glycemic excursions (MAGE), continuous overall net glycemic action (CONGA), and mean of daily differences (MODD) (Inchiostro et al., 2013) by using the FreeStyle Libre Pro system (Abbott Diabetes Care, Tokyo, Japan), a continuous glucose monitoring (CGM) system capable of providing records of glucose levels, trends, and patterns in each individual for up to 14 days. Moreover, the averaged percentage of time each participant spent in hypoglycemia (<70 mg/dL) will be also calculated.Self-reported hypoglycemic events: Participants will be assessed for hypoglycemic events by asking the following questions: “Did you experience any hypoglycemia episode that required the assistance of another person in the past year?” (Yes/No); “Did you experience any symptoms, such as sweating, palpitation, or trembling, in the past year?” (Yes/No); and “Did you experience any symptoms, such as lightheadedness, unsteadiness, dizziness, or visual disturbance, in the past year?”Microangiopathy and macroangiopathy: Participants will be assessed at baseline and at follow-up for microangiopathy including retinopathy, nephropathy, and neuropathy. Participants will be assessed for retinopathy categorized into five stages (Wilkinson et al., 2003): (1) no apparent retinopathy, (2) mild non-proliferative retinopathy, (3) moderate non-proliferative retinopathy, (4) severe non-proliferative retinopathy, (5) proliferative diabetic retinopathy. They will also be assessed for presence or absence of edema in the macula of the retina as well as for visual acuity by the Landolt Ring Test. Participants will be assessed for diabetic nephropathy categorized into five stages based on urinary albumin (mg/gCr), urinary protein (g/gCr), or estimated glomerular filtration rate (eGFR, mL/min/1.73m2) (Japan Diabetes Society, 2016): (1) Pre-nephropathy, (2) incipient nephropathy, (3) overt nephropathy, (4) kidney failure, (5) dialysis therapy. They will also be assessed for diabetic neuropathy using the Achilles tendon reflex test and vibration testing with a 128-Hz graduated tuning fork. Again, they will also be assessed for macroangiopathy, including ischemic heart disease, stroke, and peripheral vascular disease, based on their clinical charts and MR or CT imaging (Japan Diabetes Society, 2016).

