
##### Improvement in Parameters as Part of Comprehensive Geriatric Assessment (CGA)

CGA includes following specific measurements:

Basic ADL: Participants will be evaluated for basic ADL using the Barthel index (Mahoney and Barthel, 1965), which includes 10 items to assess basic self-care abilities, such as feeding, transfer from bed to chair, bathing, bowel control, and bladder control, where the score ranges from 0 (complete dependence) to 100 (complete independence).Instrumental ADL: Participants will also be assessed for instrumental ADL using the Lawton index (Lawton and Brody, 1969), which includes 8 items, such as using the telephone, shopping, and handling medication, where the score ranges from 0 (low function) to 8 (high function).Depressive symptoms: Participants will be evaluated for depressive symptoms using the 15-item Geriatric Depression Scale (Yesavage et al., 1982), where the score ranges from 0 to 15, with higher scores indicating more depressed mood.Physical performance: For all participants, usual gait speed over a distance of 2.4 m at the mid-point of the walkway that has both acceleration and deceleration zones (1 m, respectively) will be measured twice and a mean value will be calculated (Guralnik et al., 1994). Both right- and left-hand grip strengths will be measured using a standard digital hand grip dynamometer (Takei Scientific Instruments Co., Ltd, Japan) at standing position with shoulder adducted and neutrally rotated and elbow in full extension (Watanabe et al., 2005). One-leg standing tests will also be performed on all participants (Michikawa et al., 2009) using the one-leg standing test to measure how long (in seconds) each participant in bare may be able to stand unassisted on one leg as long as possible with eyes open for up to 60 s, and an average of left and right one-leg standing times will be calculated.Physical frailty and sarcopenia: Physical frailty will be defined for all participants based on the frailty phenotype proposed by Fried et al. in the Cardiovascular Health Study (Fried et al., 2001), which consists of shrinking, weakness, slowness, self-reported exhaustion, and low physical activity. In addition, to determine the presence or absence of sarcopenia (Chen et al., 2014; Cruz-Jentoft et al., 2019), appendicular muscle mass (AMM) will be measured in all participants by bioelectrical impedance analysis, and skeletal muscle mass index will be calculated as AMM divided by height squared (kg/m2).History of falls and fall risk: All participants will also be examined for any history of falls within the past 12 months. The Fall Risk Index (Kikuchi et al., 2009) consisting of 21 questions, including the following 3 subcategories, physical function (8 items), geriatric syndrome (8 items) and environmental hazards (5 items) will be used to detect their risk of falls, where each item receives a score of 1 (risk present) or 0 (risk absent), with a higher sum of scores indicating a higher risk of falls.Nutritional status: All participants will be assessed for their nutritional status using the Mini-Nutritional Assessment Short-Form (Rubenstein et al., 2001) composed of 6 questions, where the score ranges from 0 to 14, with a higher score indicating better nutritional status.Intakes of nutrients and foods: All participants will be assessed at baseline and at 18-month follow-up with the Food Frequency Questionnaire (Sasaki et al., 2003), which is designed to assess the average intake of 47 foods and beverage to estimate their daily food-group consumption and nutrient intakes.Appetite: Participants will also be assessed for their appetite using the Simplified Nutritional Appetite Questionnaire (Nakatsu et al., 2015), where the total score ranges from 4 to 20, with a higher score indicating a better appetite.Social network: The Lubben Social Network Scale 6 (Lubben et al., 2006) composed of 6 questions will be used to assess each participant's social network, where the score ranges from 0 to 30, with a higher score indicating better social network.Social participation: Participants will also be assessed for their social participation by a questioner about their social participation in eight types of groups (Kanamori et al., 2014): (1) neighborhood associations/senior citizen clubs/ fire-fighting teams (Local Community); (2) hobby groups (Hobby); (3) sports groups or clubs (Sports); (4) political organizations or groups (Politics); (5) industrial or trade associations (Industry); (6) religious organizations or groups (Religion); (7) volunteer groups (Volunteer); and (8) Others.

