##### Social Participation

To promote social participation, participants will be requested to go out at least three times a week. Moreover, participants will be requested to monitor their social activities including taking care their grand-children, doing work/volunteer work, face-to-face conversation, shopping/eating-out, and participating in organizations or groups by using a study-provided booklet every day. Again, to encourage an active lifestyle, a meeting will be heled after each physical exercise session, where participants discuss their physical, social, and cognitive activities among themselves.

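### Assisted hypoglycemia is measured by one-year recall of cognitively impaired patients, and the required study partner has no stated part in the answer

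*Protocol article*

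**What the plan says.** All references are to the protocol article.

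- **Instrument.** Under Improvement in Outcomes Related to T2DM, the outcome is labeled self-reported, and "Participants will be assessed for hypoglycemic events by asking the following questions". The first question is "Did you experience any hypoglycemia episode that required the assistance of another person in the past year", answered yes or no. Two further questions ask about symptoms over the same year.
- **Respondents.** Table 1 admits "Patients with a Japanese version of the Montreal Cognitive Assessment score of less than 26" and "Mini-Mental State Examination score, between 21 and 30". Eligibility Criteria places them in a category that runs from mild cognitive impairment to mild dementia.
- **Study partner.** Inclusion criterion 7 requires one for every patient. The only further role stated, under Eligibility Criteria, is that consent may be given through the partner.
- **Blinding.** Randomization and Blinding says that participants know their arm. Assessor blinding is stated for primary outcome data only.
- **Contact.** The intervention arm has exercise sessions at least twice a month and dietary counseling about every two months. The control arm has usual care plus general instructions at baseline.
- **Other sources on hypoglycemia.** Continuous glucose monitoring (CGM) gives the percentage of time below 70 mg/dL in both arms, for up to 14 days, at baseline and 18 months. Adverse events are monitored throughout.

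**The concern.** The item asks patients selected for cognitive impairment to look back over a year. Memory is also a domain of the primary composite, so the trial tests whether a faculty on which this answer depends changes by arm. An assisted episode has, by definition, a second witness, and the trial already requires a partner who may be that witness or may know of the episode. Nothing says that the partner is asked.

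Two things are at stake. Under-reporting that is equal in the arms shrinks the absolute difference and costs power. Reporting that differs by arm biases the comparison itself, and the open-label design with unequal contact makes such a difference possible. The outcome matters to the trial's own argument: the Introduction treats severe hypoglycemia as a hazard for cognition, cardiovascular events and mortality, and the Interventions section uses CGM in the intervention arm to avoid hypoglycemia.

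**Working it through.** **No figure to reproduce.** The article gives no event rate, recall accuracy or power for this outcome. The risks and recall sensitivities below are assumptions. Only the number per arm comes from the article: 300 randomized, less 20% dropout, split 1:1, is 300 × 0.80 / 2 = 120.

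**Model.** Observed risk = true risk × recall sensitivity, assuming no false positives. Hence observed risk ratio = true risk ratio × (sensitivity in intervention / sensitivity in control).

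**Step 1: size of distortion.** Assumed true risk is 20% in controls. In the intervention arm it is 14% (true RR 0.70, difference 6 points) or 20% (no effect).

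| Recall, control / intervention | True 20% vs 14% is seen as | No effect is seen as |
|---|---|---|
| 50% / 50% | 0.10 vs 0.07: RR 0.70, 3 points | RR 1.00 |
| 50% / 60% | 0.10 vs 0.084: RR 0.84, 1.6 points | 0.12 / 0.10 = RR 1.20 |
| 60% / 50% | 0.12 vs 0.07: RR 0.58, 5 points | 0.10 / 0.12 = RR 0.83 |

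Equal under-recall leaves the ratio alone and halves the difference. Unequal recall moves the ratio either way.

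**Step 2: power under equal under-recall**, 120 per arm, two-sided 5%.

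- True 30% vs 15%: 80% with full recall, 61% at sensitivity 0.7, 45% at 0.5.
- True 10% vs 5%: 31%, 23% and 17%. At low event rates, power is poor even with perfect recall.

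**Step 3: a wide gap in recall**, 60% in controls and 90% in the intervention arm.

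- True 30% vs 20% is seen as 0.30 × 0.6 = 0.18 vs 0.20 × 0.9 = 0.18, so a true RR of 0.67 appears as 1.00.
- With no true effect, the observed RR is 0.9 / 0.6 = 1.50. A significant excess in the intervention arm appears in about 14%, 25% and 39% of trials at true risks of 10%, 20% and 30%, against a nominal 2.5% in that direction.

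**Step 4: what a partner report would do.** If patient and partner errors are independent, the sensitivity of a report from either is 1 − (1 − patient)(1 − partner). Take patient recall of 50% in controls and 60% in the intervention arm.

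- Partner 70% in both arms: 1 − 0.5 × 0.3 = 0.85 and 1 − 0.4 × 0.3 = 0.88. No effect is seen as RR 0.88 / 0.85 = 1.04 instead of 1.20.
- Partner 50% in controls and 70% in the intervention arm: 1 − 0.5 × 0.5 = 0.75 and 0.88. No effect is seen as RR 0.88 / 0.75 = 1.17.

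Asking the partner raises sensitivity in each case. It removes most of the difference by arm only if partners report alike in both arms.

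**The case against.** **Other safeguards exist.** CGM does not depend on memory and is done in both arms. All adverse events are monitored with onset, severity and treatment, on-site monitoring checks that they are reported, and their frequencies are compared between arms. This stands in part. CGM covers two windows of up to 14 days and yields time below a threshold, not assisted episodes over a year. Adverse event reports have no stated informant and no stated link to this outcome, and unequal contact could affect them too.

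**The article is condensed.** A partner role may be set out in the full protocol, which is not shown, and that cannot be excluded. But the article does fix the label, the wording and the one-year window, so the point rests on a stated choice.

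**The numbers are assumed, and the model allows no false positives.** Both are true. The model fits the assisted-episode item better than the two symptom questions, which are non-specific, so the point is limited to the former.

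**Stronger readings that a reader might infer, and that the article does not support:**

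- *Falls suffer from the same fault.* The article says only "All participants will also be examined for any history of falls within the past 12 months". It names no informant, so patient-only recall is a guess.
- *Intervention diaries prompt recall of events.* The booklets and diaries cover exercise, weight, meals, dietary variety and social activity. None is said to record hypoglycemia.
- *The intervention is tighter metabolic management with hypoglycemia as its main harm.* Both arms follow the same guideline. The stated metabolic difference is that clinicians see the CGM results in the intervention arm only.
- *The bias will show a false harm.* Participants in an open-label trial could over-report or under-report.

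**Conclusion.** The point holds for the assisted-hypoglycemia item. One-year recall by patients selected for cognitive impairment is a weak sole source when a partner is already required. Under-reporting is likely, though the article does not demonstrate it. Reporting can differ by arm, in a direction that cannot be determined from the text.

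The illustrations show that a recall gap of 10 percentage points can move a null risk ratio to 1.20 or 0.83, and that equal recall of 50% halves the risk difference. They rest entirely on assumed risks and sensitivities and on no false positives. Only a secondary outcome is affected. The primary composite, its analysis and the sample size are untouched. This is a cheap improvement in method and not a correction of an error or contradiction.

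**What to change.** Put the hypoglycemia-with-assistance question to the patient and the study partner together, in the same way in both arms, at baseline, 6 and 18 months. Record both answers. Analyze an event as present if either reports it, and keep the patient-only answer as a sensitivity analysis. If the full protocol already gives the partner this role, say so in the outcome definition.

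The cost is an instruction on the case report form and a few minutes with someone whom the trial already requires. There are three downsides. Counting a report from either person admits some false positives. Partners who do not live with the patient may know less. Nothing says that partners are blinded, so reporting that differs by arm is reduced but not removed.

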## Methods and Materials

### Study Design and Setting

The J-MIND-Diabetes study was designed as a 18-month, open-labeled, randomized, controlled, multicenter trial of multi-domain intervention targeting modifiable risk factors for dementia among T2DM patients with cognitive impairment. To be organized by a central coordinating center at the National Center for Geriatrics and Gerontology (NCGG), this study involves 16 centers located in Japan. This study will randomize 300 T2DM patients with cognitive impairment into intervention or control groups. The multi-domain intervention will address the following 4 domains: (1) management of metabolic and vascular risk factors (diabetes, hypertension, and dyslipidemia); (2) physical exercise and self-monitoring of physical activity; (3) nutritional guidance; and (4) promoting social participation. The control group will receive usual diabetes care and general instructions on dementia prevention. The primary and secondary outcomes will be assessed at baseline, 6, and 18 months in both groups (see the study flow diagram shown in Figure 1).

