#### Assessment

All subjects will complete neuropsychological tests, comprehensive geriatric assessments (CGA), and blood and urinary tests at baseline, as well as at 6- and 18-month follow-up. Additionally, brain MRI or CT will be performed by the scanner available at each institution at baseline and 18-month follow-up to detect any local lesion such as cerebral infarctions that can greatly affect cognitive function. Adherence to the intervention programs and adverse events will be also monitored during this trial. The timeline for scheduled assessments following the SPIRIT guidelines is shown in Figure 2.

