**Figure 2 F2:**
[figure not shown]
Timeline for participants in the J-MIND-Diabetes trial. ^*^: Non-mandatory, -t_1_: visit within 8-week before the day of allocation, t_1_…t_n_: visit to the hospital during the study period. CT, computed tomography; J-MIND-Diabetes, japan-multi-domain intervention trial for prevention of dementia in older adults with diabetes; MRI, magnetic resonance imaging; SPECT, single photon emission computed tomography.

Psychologists at each institution were trained in the implementation and scoring methods of neuropsychological tests by participating in the training session held at the NCGG. Moreover, scoring for the Rey-Osterrieth Complex Figure Test (ROCFT) (Strauss et al., 2006) will be conducted by a single psychologist from the NCGG to minimize variability in scoring between neuropsychologists.

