#### Adverse Events and Serious Adverse Events

To evaluate the safety of the intervention, all adverse events and serious adverse events will be monitored during this trial. Information to be collected about adverse events will include their date of onset, severity, associated treatment, consequences, and causation. Serious adverse events will be reported to the principal investigator, IRB, and co-researchers immediately.

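### At month 6 the falls item, and the hypoglycaemia questions if asked then, recall 12 months, half of them before randomisation, which about halves the relative contrast at that visit

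*Protocol article*

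**What the plan says.** All references are to the Protocol article.

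- *Improvement in Outcomes Related to T2DM* prints three self-report questions, all with a one-year recall. The first is "Did you experience any hypoglycemia episode that required the assistance of another person in the past year"; the second is "Did you experience any symptoms, such as sweating, palpitation, or trembling, in the past year". The third asks in the same way about lightheadedness, unsteadiness, dizziness or visual disturbance. No visit schedule is given for these questions.
- *Improvement in Parameters as Part of Comprehensive Geriatric Assessment (CGA)*: "All participants will also be examined for any history of falls within the past 12 months".
- *Study Design and Setting*: "The primary and secondary outcomes will be assessed at baseline, 6, and 18 months in both groups".
- *Assessment*: all subjects complete "comprehensive geriatric assessments (CGA), and blood and urinary tests at baseline, as well as at 6- and 18-month follow-up". The falls item belongs to the CGA.
- *Figure 2* (legend) places the baseline assessment at a "visit within 8-week before the day of allocation".
- *Adverse Events and Serious Adverse Events*: "all adverse events and serious adverse events will be monitored during this trial", and "Information to be collected about adverse events will include their date of onset, severity, associated treatment, consequences, and causation".
- *Data Analyses* assigns secondary categorical variables to logistic regression or chi-squared tests and does not mention the recall window.

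No shorter recall period is stated for the 6-month visit.

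**The concern.** A fixed 12-month recall suits the baseline visit and the month-18 visit, which follows the previous one by 12 months. It does not suit a visit six months after randomisation. A 'Yes' at month 6 may refer to an event before allocation, and a Yes/No answer cannot show which. Randomisation makes the earlier history similar in the two arms on average, so it adds events to both and pulls the ratio towards 1.

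The period affected is the first six months of the programme, when the exercise sessions, counselling and CGM-informed management begin. The article's Introduction treats severe hypoglycaemia as a risk in its own right, and its *Interventions Procedures* give avoidance of hypoglycaemia as the purpose of CGM in the intervention arm. An early benefit or harm on these outcomes is therefore of interest. The CGM outcome measures do not fill the gap, because they are scheduled at baseline and 18 months only.

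**Working it through.** **The plan's own figure.** The article gives no event rate or power for hypoglycaemia or falls. Its only size calculation is for MMSE change: (2.58² + 3.55²) × (1.960 + 0.842)² / 1.12² = 120.5, so 121 per arm and 242 in total, as stated. Dividing by 0.85 and 0.80 gives 285 and 303, consistent with 300. None of this depends on the recall window.

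**Window coverage**, taking the visits as exactly 6 and 18 months after randomisation:

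| Visit | 12-month recall covers | Share before randomisation |
|---|---|---|
| Month 6 | months -6 to +6 | 6/12 = 50% |
| Month 18 | months +6 to +18 | 0% |

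Months 0-6 appear only in the mixed window.

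**Model.** Events occur at a constant control rate λ per year. The intervention arm has rate λ before randomisation and λ·RR afterwards. The rate ratio over the mixed window is (0.5λ + 0.5λ·RR)/λ = (1 + RR)/2. A true 0.7 is seen as 0.85, 0.5 as 0.75 and 2.0 as 1.5, so the relative excess or reduction in rate is exactly halved.

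**Worked example** (assumptions, not from the article: λ = 0.3 per year, RR = 0.7):

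- Mixed window as written: control 1 - exp(-0.30) = 25.9%; intervention 1 - exp(-0.15 - 0.105) = 22.5%. Risk ratio 0.87, difference 3.4 points.
- Clean 6-month window: control 1 - exp(-0.15) = 13.9%; intervention 1 - exp(-0.105) = 10.0%. Risk ratio 0.72, difference 4.0 points.

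Sample per arm at 80% power and two-sided 5%, n = (1.960 + 0.842)² × [p₁(1-p₁) + p₂(1-p₂)] / (p₁-p₂)², using unrounded risks:

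- Mixed: 7.85 × (0.1920 + 0.1744) / 0.0341² ≈ 2,470.
- Clean: 7.85 × (0.1199 + 0.0898) / 0.0396² ≈ 1,050.
- Ratio 2,470 / 1,050 ≈ 2.4.

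**Absolute scale.** The mixed difference divided by the clean 6-month difference equals exp(-λ/2), whatever RR is. In the example this is exp(-0.15) = 0.86, so 86% of the absolute difference is kept. Power falls mainly because the added events raise the variance.

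**Range** (assumed control 12-month risk 2% to 40%, RR 0.5 or 2.0): the log risk ratio in the mixed window is 0.36 to 0.58 of that in the clean window, and the absolute difference keeps 77% to 99% of its size. At 20% control risk and 150 per arm, power is 18% mixed against 37% clean for RR 0.5, and 40% against 62% for RR 2.0.

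**The case against.** Five points can be made on the other side.

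1. **Safety is assessed elsewhere.** A reader might infer that the trial's safety comparison is halved. The article does not support that. Safety is evaluated by monitoring adverse events with onset dates, compared by chi-squared or Fisher's exact test, and a dated event in months 0-6 is not mixed with earlier history. This stands. The article does not, however, say that hypoglycaemia or falls are actively solicited as adverse events, so those records may not replace the questions.
2. **The final visit is clean.** The month-18 window lies wholly after randomisation, and 18 months is the primary time point. A reading that dilution runs through follow-up is wrong. This stands, but month 18 does not cover months 0-6.
3. **Month-6 use of the hypoglycaemia questions is inferred.** The general schedule is not literally true of every secondary outcome: the CGM measures and the Food Frequency Questionnaire are at baseline and 18 months only. Figure 2 is not shown, and visit-specific form wording may sit in the full protocol. This lowers confidence for hypoglycaemia. For falls, the CGA schedule names month 6 directly.
4. **The loss is easily overstated.** Halving the relative effect might suggest a fourfold sample. A ratio of about 4.4 arises only against a full post-randomisation year, which cannot exist at month 6. In the worked example, power at 150 per arm is only about 10% as written and about 18% with a clean window. This stands: the gain is mainly an interpretable estimate, not a well-powered test.
5. **Symptom wording.** The two symptom questions, as printed, do not mention low blood sugar, so one might infer that exertion in the exercising arm will be counted as hypoglycaemia. That is plausible in an open-label trial, but the questions are introduced as assessing hypoglycaemic events, only English text is shown, and nothing quantifies it. It is a secondary remark.

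**Conclusion.** The point holds for the month-6 self-reported outcomes: firmly for falls, and for hypoglycaemia if the questions are asked then as the general schedule implies. Followed as written, half of the recall window precedes randomisation and the relative contrast at that visit is about halved. In the worked example the risk ratio moves from 0.72 to 0.87, with 86% of the absolute difference kept and about 2.4 times the sample needed.

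These sizes rest on a constant event rate, accurate recall, equal pre-randomisation rates in the arms, and assumed event rates, since the article gives none. The 50% share needs only the printed recall period and a visit six months after randomisation. The month-18 result, the adverse event comparison, the primary outcome and the sample size are not affected.

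**What to change.** Give each visit its own recall window:

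- **Baseline:** keep the past-year wording, and use the answer only as a covariate.
- **Month 6:** ask about the time since the participant was allocated to a group. Asking since the last study visit would not do, because baseline may be up to 8 weeks before allocation. With 26 weeks of follow-up, up to 8/34 = 24% of that window would still precede randomisation.
- **Month 18:** ask about the time since the month-6 visit.
- **Analysis:** compare cumulative post-randomisation occurrence, combining months 0-6 and 6-18.
- **Optional:** tie the two symptom questions to low blood sugar.
- **Clarify** whether the hypoglycaemia questions are asked at month 6.

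If the data are already collected, label the month-6 result as partly pre-randomisation, base the between-arm comparison on month 18, and use dated adverse event records for months 0-6.

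The cost is a questionnaire wording change and a minor amendment. The baseline and month-6 windows will differ in length, so within-person change between them is not directly comparable. The comparison between arms is not harmed, because both arms share the same window at each visit.
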